### Data monitoring and recording

A Data Monitoring Committee (DMC) is not established as there is no blinding and adverse events can be reported directly to the study staff. All aspects of the intervention are part of the conventional nursing care of incontinence. There are no interim analyses planned and all results will be analysed after the data collection is completed.

### Statistical methods

The data material will be analysed using SPSS. The focus of the evaluation will be on descriptive analyses and correlation analyses. Conclusively, the results will be evaluated and presented in a stratified manner. The following methods will be used to answer the research questions: Regression analyses, MANOVA with measurement repetition, correlation analysis, multilevel analysis and chi-squared tests. The results of the qualitative interviews will first be transcribed and then analysed using qualitative contents analysis [52] and MAXQDA software.

### Logistical implementation of the study project

In the context of the RCT, in addition to the technical and methodological points, the underlying logistical process must also be comprehensively defined and coordinated with the project partners involved so that regular nursing care is not restricted at any time. Therefore, after randomization of the sample into intervention and control group, detailed micturition profiles of the participating residents are additionally established by the incontinence care provider responsible for the respective nursing facility. The ICM requirements will be reported to the ICM manufacturer. Concerning the intervention group, AssistMe obtains the personal ICM requirements for a usage time period of four to six weeks as well as the ICM from the ICM manufacturer. AssistMe then attaches the digital incontinence sensors to the ICM and sends the material to the according nursing facility. In parallel, the ICM manufacturer delivers the original ICM requirement to the nursing facilities to ensure that the supply is not limited at any point. This will be particularly effective if the RCT has to be paused or ended due to dropout criteria. This will ensure that the standard care can be resumed at any time, independent of the digital incontinence management (see Fig. 4).

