#### Secondary target group

Since nursing staff is to incorporate and evaluate the digital assistance system as part of their professional activities, only the nursing staff responsible for incontinence care is included in the study. By doing so, differentiated statements about the system can be voiced by the nursing staff. Ideally, the included nursing staff is also responsible for participants in the control group, enabling them to identify and describe any changes concerning nursing care with an even greater nuance. Furthermore, a written consent to participate in the study after being informed and educated is necessary. In addition, nursing staff with similar as well as different characteristics such as professional experience, age and gender is included. Thereby, the individuals should differ as minimally and maximally as possible. This contrastive sampling procedure intendeds to reflect the heterogeneity of the research subject through the selection of individuals to be interviewed [38].

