The digital assistance system from AssistMe GmbH provides the responsible nursing staff within the care facilities with an automated message concerning the status of the incontinence material (ICM) of the home residents within the IG. The status report does not give any indication about whether the ICM needs to be changed but only describes the status of the ICM itself (for example, 1st urination, 2nd urination, 3rd urination). The decision to change the ICM is made by the responsible nursing staff and not by the digital assistance system from AssistMe GmbH. In addition, it is possible to store individual incontinence profiles of the home residents in order to obtain an additional source of information concerning the decision among the nursing staff as to when an optimal change of the ICM should take place.

The digital assistance system from AssistMe GmbH is to be understood as a supporting, digital measure in the context of incontinence management.

The technical procedure of the intervention is divided into three phases:Preparation and implementation phaseTraining and testing phaseRealisation phase

(1) Preparation and implementation phase

This thus implies, on the one hand, the implementation of an IT infrastructure within the care facility and the associated assurance of a complete connectivity of the wearables (explanation, follows below) equipped to the ICM with the network. On the other hand, the logistical process of the ICM requirements for the home residents will be jointly coordinated in detail with the respective care facilities and service providers (TZMO and geria + med) so that a) no supply bottlenecks arise and b) the study process can be realized as smoothly as possible.

(2) Training and testing phase

The training and testing phase is used to familiarise the participating nursing staff with the digital assistance system from AssistMe GmbH. This means both a multi-hour training session for nursing staff and a 1–2 week trial period to "get to know" and "better understand" the system will be conducted, in order to reduce any technical challenges during the course of the study and to address any questions that arise from the nursing staff in advance.

(3) Realisation phase

The realisation phase represents the actual RCT and intervention. In this phase the digital assistance system is connected within the nursing facility, the nursing staff has been trained and the study project begins (see Fig. 2).

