### Recruitment

#### Primary target group

The recruitment procedure is divided into two phases: 1) The study staff of the Neubrandenburg University of Applied Sciences and those responsible from AssistMe will visit the participating inpatient nursing facilities. In an open event all residents of the facility who are interested will be informed about the RCT (including the aims of the study, procedure and the intervention). This is meant as opportunity to ask questions to the persons responsible for the RCT. This shall emphasise the absolute voluntary nature of study participation. 2) If the residents or their family caregivers/legal guardians indicate interest in participating in the study, they inform the responsible nursing staff in the facility. The nursing staff consolidate the interested parties and forward their names to the study staff at the Neubrandenburg University of Applied Sciences. The study staff then visits the interested parties again. In a conversation, they will be again informed in detail about the RCT as well as the intervention. In addition, the inclusion and exclusion criteria will be checked. Residents who meet the eligibility criteria and who would like to participate in the RCT are then examined regarding their cognitive performance using the Mini Mental Status Examination (MMSE). Depending on their score, they are assigned to the respective strata "cognitively impaired" or "not cognitively impaired." Subsequently, both subgroups are randomized individually into the intervention and control group.

Should individuals in the primary target group drop out of the RCT prematurely (e.g., due to compelling medical or nursing reasons), new particpipants will be recruited and included if they meet the inclusion criteria. This post-recruitment is foreseen up to a maximum of two months after the start of the system test period.

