### Blinding

The study information for participants includes information about the assigned arms and the randomised design of the study. An independent researcher not involved in the study performs the allocation using Excel. Participants, nursing staff, the provider of the digital assistance system and research study staff will not be blinded to the group assignment.

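### Micturition profiles and pad requirements are settled only after randomisation in an open trial, so material consumption, a secondary endpoint, could differ by arm for reasons other than the sensor

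*Protocol article*

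**What the plan says.** All references are to the Protocol article.

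- **Order of steps.** Recruitment (Primary target group) places the eligibility check and the MMSE before allocation: "Subsequently, both subgroups are randomized individually into the intervention and control group". Logistical implementation of the study project then states that "after randomization of the sample into intervention and control group, detailed micturition profiles of the participating residents are additionally established by the incontinence care provider". This sentence is not limited to one arm.
- **What follows the profile.** The next sentence reads "The ICM requirements will be reported to the ICM manufacturer". The route then divides: "Concerning the intervention group, AssistMe obtains the personal ICM requirements for a usage time period of four to six weeks", attaches the sensors and ships the material to the home. As a safeguard for supply, "In parallel, the ICM manufacturer delivers the original ICM requirement to the nursing facilities".
- **Blinding.** "Participants, nursing staff, the provider of the digital assistance system and research study staff will not be blinded to the group assignment". The incontinence care provider, who makes the profile, is not in this list.
- **Endpoint.** Endpoints lists consumption of incontinence material as secondary, and Table 1 measures it by complete documentation of usage.
- **Control.** Methods and design defines the control group only by the absence of the digital system. The profile is not mentioned there.
- **Staff.** Inclusion criteria (Secondary target group) says: "Ideally, the included nursing staff is also responsible for participants in the control group".

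**The concern.** A step that leads to each resident's material requirement is placed after the arm is known, in a trial with no blinding, although material use is one of the outcomes. If the provider draws up the profile or the requirement with the arm in mind, the arms may start with different requirements. Someone who expects the sensor to save material might, for example, set a leaner requirement for sensor residents. Part of any observed difference in consumption would then come from how the requirement was set and not from the sensor. The protocol's Discussion in the abstract expects fewer unnecessary changes of material, so this is an outcome on which the trial hopes to show a benefit.

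A lesser matter is description. If all participants receive an additional profile, the comparison is between the sensor system and usual care plus a profile, and the definition of the control group does not say so.

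**Working it through.** The only calculation in the plan is the sample size for falls. There is no planning figure for material consumption, so there is nothing to reproduce for this endpoint. The check is one of sequence and logic.

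**1. Sequence as written.** Eligibility (severity judged from recorded material consumption) → MMSE → stratum → randomisation → micturition profile → material requirement reported → for the intervention group, material sent for sensor attachment. The text does not say where t0 falls relative to profiling. Nor does it say outright that the requirement is computed from the profile; the order of the sentences makes that the natural reading.

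**2. Which steps need the allocation?** Sensor attachment and the intervention group's delivery route do. A profile and a requirement describe the resident and do not depend on the arm. The protocol gives no reason for delaying them.

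**3. Who knows the arm?** Four parties are declared unblinded. The incontinence care provider is not named, but no text keeps the allocation from that provider, and the supply route splits by arm as soon as the requirement is known. Knowledge of allocation is therefore probable, but it is an inference.

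**4. Link to the endpoint.** Let S be the true sensor effect on mean documented usage, R the difference between arms in mean requirement caused by knowing the arm, and k the share of a requirement difference that carries through to usage. Then:

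observed difference = S + k × R

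- If R = 0, or if k = 0, the observed difference estimates S.
- If both are non-zero, it is off by k × R, with the sign of R when k is positive.
- The documents give neither R nor k, so the error can be neither sized nor signed. At full carry-through (k = 1) it equals R; with no carry-through it is zero.

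**5. Effect of reordering.** If profile and requirement are complete before randomisation, the arm cannot influence the initial requirement. R is then zero by design, and any remaining imbalance is chance and can be described as a baseline variable.

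**The case against.** **The strongest reply** is that ordering and using are different things. The endpoint is documented usage, nurses decide each change (Interventions), and the original requirement is delivered in parallel. A different order need not become different usage. This stands: k may be well below 1, and it cannot be said that an arm difference in requirement passes in full into consumption. It does not show that k is zero. The phrase about the original requirement also leaves open whether an earlier order continues.

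**Stronger readings that a reader might infer, and that the text does not support:**

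- *Controls do not receive usual care.* Possible harms assures standard care for all participants. The text supports usual care plus an additional profile, and does not say that control residents' changes are timed by it.
- *Controls receive a component of the intervention.* Interventions says that "it is possible to store individual incontinence profiles of the home residents in order to obtain an additional source of information", but no passage equates that stored profile with the provider's micturition profile.
- *The profile itself biases the comparison.* A profile made in the same way in both arms is shared background care. Only a profile or requirement made differently by arm is a problem.
- *Power for falls is lost.* Shrinking the planned difference (2.22 − 1.65 = 0.57) by an assumed carry-over lowers power arithmetically, but the share would be invented, and no documented route runs from profiling to falls.
- *The preference for shared nurses should be deleted.* Residents are randomised individually, with 20 residents and six to eight recruited nurses per home, so deletion would not separate the staff. Dedicated nurses per arm would confound nurse with arm. The preference also serves the qualitative strand. Dilution through shared nurses is possible and deserves acknowledgement, but its size is unknown.

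**Conclusion.** The point holds in a limited form. The protocol places profiling and the reporting of material requirements after allocation in an open trial, when neither step needs the allocation. This leaves an avoidable route by which material consumption could differ between arms without any sensor effect.

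The conclusion rests on three readings: that the requirement follows from the profile, that the care provider is likely to know the arm, and that a different requirement can influence usage to some degree. All three are reasonable, but none is stated outright. Size and direction cannot be derived from the document. The point concerns one secondary endpoint; no effect on falls is established. It justifies a change because the change is small, not because a large bias has been shown.

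**What to change.** - **Recruitment (Primary target group) and Logistical implementation of the study project:** complete the micturition profile and the material requirement for every eligible resident before randomisation and before t0. Apply the same order to replacement participants recruited after the start. Leave only sensor attachment and the intervention group's supply route until after allocation.
- **Methods and design:** describe the control as usual care plus a micturition profile, without the digital system.
- **Inclusion criteria (Secondary target group):** keep the staffing preference, and acknowledge that sharing nurses under individual randomisation may dilute the contrast between arms.

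**Cost.** The profile is already planned for the participating residents, so this reorders existing work. The downside is a short interval between profiling and allocation, whose length cannot be given because the document states no profiling duration. Some profiles may also be made for residents who withdraw before being randomised.

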**Fig. 4 Fig4:**
[figure not shown]
Logistical process of the ICM supply within the study project

### Possible harms

The project partner AssistMe GmbH has already coducted numerous tests of the digital assistance system for incontinence care in the past. Harm due to heat through the sensor or other personally hazardous technical malfunctions can be ruled out.

To ensure that the system and the app function without interference, technical devices with electromagnetic emissions in microwave range are installed within the inpatient care facility (router, charger, node). Damage or incidents due to electromagnetic exposure or compatibility problems are not to be expected, as all necessary electromagnetic safety checks (electromagnetic compatibility) have been carried out and the specifications are fully met by AssistMe GmbH. The tests also showed no restrictions for the participants with regard to freedom of movement or wearing comfort of the ICM. Further comfort tests are currently being carried out to determine whether patients experience unpleasant pressure sensations from the sensor attached to the incontinence material when lying in certain positions (especially in the prone position). However, significant problems are not expected due to the small size and height of the sensor. Regarding the quality of the care, no deterioration is expected since the digital assistance system will only complement traditional nursing measures as part of incontinence care but shall by no means replace them. Standard care is assured for all participants. If problems with the system should develop, those affected in the intervention group can immediately switch to standard care.

In rare cases, participants in both target groups may experience psychological discomfort. On the one hand, this may be due to the fundamental topic of incontinence and incontinence care, which is often still a taboo subject in society. On the other hand, the sensors on the incontinence material record data continuously (24/7), which may result in an unpleasant feeling of being monitored. Particularly in the case of nursing staff, the impression could arise that they may be checked for possible nursing fails. These potential negative perceptions should be countered with transparent information at the beginning of the study as well as with close-meshed discussions with the persons concerned if necessary.

In addition, the secondary target group may also experience a time burden and technical overload, as they are expected to use and apply a new care system in parallel to the standard care of incontinence. Especially at the beginning of the study, when there is no experience in using the assistance system yet, or in already stressful situations in the daily work of the nursing staff, the use of the system could rather be perceived as a burden. These expected impairments are to be countered on the one hand with an intensive explanation of the handling and use of the system, and on the other hand with close-meshed conversations in the case of perceived challenges, especially in the first weeks of the study. Basically, all problems and wishes expressed by both target groups are taken very seriously by the study staff, and they are always responded to promptly.

A further risk could be the occurrence of COVID cases in the care facilities, whereby the facilities or the care personnel may wish to withdraw from participation due to the time required for the study project, or further participation is only possible under more difficult conditions.

Furthermore, there may be unwanted consequences for the study project from an environmental perspective due to the single use of the sensors. As part of the study project, resource-efficient production as well as the possibility of multiple use will be tested. In this regard, the study project aims to find ways to enable a multiple use or sustainable mass production of the incontinence sensors. As part of the project, indications for a more favorable mass production and/or multiple use of the sensor will be developed.

### Audit

All funds and invoices will be managed by study-independent employees in the administration of the University of Applied Sciences Neubrandenburg.

### Distribution

The study results will be made available to the scientific public through conferences and international journals, and to the general public through presentations in healthcare organizations and national congresses. In the long term, the project is intended to contribute to the further development of new quality-assured forms of care and action in nursing practice.

## Discussion

The results of the RCT are expected to provide reliable data regarding improved incontinence care. The focus is primarily on the possible improvement of the quality of life and dignity of those affected, as they are severely impacted by the taboo that often surrounds the issue and by additional health problems associated with incontinence (including falls) [4]. The study results should also show positive effects on the quality of sleep of those affected, which is often very low due to the nature of the condition and the unnecessary changes of incontinence material at night [14]. The use of a sensor-based assistance system for incontinence care could help to significantly reduce the vulnerability of those affected and the use of force when changing the incontinence material [10]. Since progressive urinary and faecal incontinence as well as the associated excessive demands in dealing with it are not uncommon reasons for entering inpatient care, a reliable and easy-to-use digital assistance system could help to relieve the burden on family caregivers and give those affected the opportunity to remain in their homes longer than before [53].

In addition, data will be determined as to whether and how processes in inpatient care settings can be improved using a digital assistance system. In the long term, the use of digital assistance systems for incontinence care may lead to new nursing and care concepts that support inpatient long-term care. The results of the study are to be processed in form of recommendations for action and to provide information on possible transferability to standard care. Focal points are:conceptual elaboration concerning nursing facilities with recommendations for data protectioninformation of those in need of caretechnical implementation, use and maintenance of the digital assistance systemcleaning and disposal of the sensor technologynursing staff training

Another focus is on economic feasibility studies, which consider implementation and transfer to care settings in inpatient facilities even after the end of the funding period. For outpatient services, the study also provides information on the application and implementation of the digital assistance system.

## Data Availability

The raw datasets can be obtained from the corresponding author upon justified request.

## Abbreviations

BLE: Bluetooth Low Energy
CG: Control group
DMC: Data Monitoring Committee
DNQP: German Network for Quality Development in Nursing
eCRF: Electronic case report forms
GKV-Spitzenverband: German National Association of Statutory Health Insurance Funds
HSNB: University of Applied Sciences Neubrandenburg
ICM: Incontinence material
ID: Identification number
IG: Intervention group
LTE: Long Term Evolution
MMSE: Mini Mental Status Examination
RCT: Randomized controlled trial
SPIRIT 2013 Statement: Defining standard protocol items for clinical trials
SPSS: Statistical Package for the Social Sciences
TA-EG: Questionnaire to measure the affinity for technology scale
